**4.1 Interim analyses**

No interim analyses are being planned.

**4.2 Methods for additional analyses (e.g., subgroup analyses)**

No subgroup analyses will be conducted.

**4.3 Analytic methods for handling protocol nonadherence and statistical methods for handling missing data**

We anticipate minimal missing data (<10%) for the primary outcome given that all participants will be in patients with regular daily contact maintained during treatment. The evaluation of missing data effects will involve comparing differences under plausible and extreme missing data scenarios. In the event of a significant primary test result, we will also assess the interaction size between group assignment and missing data necessary to render the difference nonsignificant. Should 10% or more of the baseline samples be excluded due to missing data, we will apply multiple imputation techniques for comprehensive analysis.

**5 Technology roadmap**

The study protocol’s flowchart is outlined in Fig. 2.

[figure not shown]

Fig. 2. Participant flowchart for cardiovascular ultrasound therapy

**6 Adverse events**

**6.1 Adverse events reporting and harms**

All adverse events, defined as any unfavorable or unintended reactions to the intervention, will be meticulously documented based on patient-reported symptoms and observational assessments during each visit. To date, no adverse events have been reported with use of the cardiovascular ultrasound therapy regimen in cardiovascular disease. Potential mild adverse reactions—including mild local swelling, heightened local pain response, and altered local sensitivity—will be monitored closely. In the event of such symptoms, prompt and suitable symptomatic treatment will be administered.

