**3.7.2 Intervention description**

Participants allocated to the intervention group will undergo a 10-day regimen utilizing a medical cardiovascular ultrasound therapy device (838C-M-L-I/II, Shenzhen, China). The ultrasound instrument is equipped with a sound head comprising five transducer units operating at an ultrasonic frequency of 0.84 MHz with a sound intensity range of 1 W/cm^2^–1.25 W/cm^2^. The therapeutic ultrasound sessions require a controlled environmental temperature. Patients will assume the supine position, exposing the precordial region, with the 5-pronged head positioned parallel to the heart’s long axis; it should cover the entire precordial region including the right and left coronary arterial trunks and the aortic root (Fig.1). The five transducer units function sequentially in a scanning pattern, with each unit operating for 5 seconds and transitioning with a 0.5-second interval, following a clockwise rotation until the treatment has been completed. The cardiovascular ultrasound therapy device operates in a pulsed mode, and each treatment session lasts for 20 minutes; there would be two daily sessions for a total of 20 treatments. The control group was not given extracorporeal cardiac ultrasound therapy. Participants in the control group will not receive cardiovascular ultrasound therapy. cardiovascular ultrasound therapy will be assessed at baseline (24th-hour post-PCI), on the 10th day, and at the end of the first and third months post-intervention. If it is necessary to change the medication regimen as much as possible, if it is necessary to change the medication regimen, it should be decided after evaluation by the investigator, and if the medication regimen that does need to be changed has an impact on the test results, the patient should be excluded and the reasons for changing the medication regimen should be recorded in detail.

[figure not shown]

Fig. 1. Diagram of ultrasound head placement.

A: Patients undergoing cardiovascular ultrasound therapy. B is used in patients with occlusion of one coronary artery and C is used in patients with occlusion of both coronary arteries.

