**6.3 Methods for recording and reporting adverse events**

(1) The investigator should explain to the patient that it is necessary to truthfully reflect the changes in the condition after taking LIPUS and avoid inducing questions.

(2) While observing the efficacy, pay close attention to the observation of adverse reactions or unexpected toxic side effects (including symptoms, signs, laboratory examinations), regardless of whether they are related to LIPUS or not, should be recorded in detail, and the causes should be analyzed, judgments should be made, and follow-up observation and records should be followed. The incidence of adverse reactions should be counted.

(3) For adverse reactions occurring during the study, the symptoms, severity, occurrence time, duration, treatment measures, and process should be recorded in the study medical record, and their relevance to LIPUS treatment should be evaluated, and recorded in detail by the investigator, signed and dated.

(4) When adverse reactions are found, the observer physician can decide whether to suspend the observation according to the condition, and the cases that withdraw from the trial due to adverse reactions should be followed up and investigated, and the treatment process and results should be recorded in detail.

(5) If there is a serious adverse event in the study, the unit undertaking the clinical study must take immediate measures to protect the safety of the subjects and report to the sponsor within 24 hours or no later than the 2nd working day. The Sponsor will ensure that all reporting procedures required by laws and regulations are met.

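### Section 6.1 defines adverse events as reactions to the intervention, which does not fit an untreated control arm and contradicts 6.3(2), so events may be ascertained and counted unequally between arms

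*Protocol*

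**What the plan says.** Section 6.1 covers all adverse events, "defined as any unfavorable or unintended reactions to the intervention". It says these "will be meticulously documented based on patient-reported symptoms and observational assessments during each visit", without restricting this to one arm. Section 3.7.2 states: "Participants in the control group will not receive cardiovascular ultrasound therapy". No sham is described.

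Section 6.3 uses different terms from item to item:

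- Item (1): patients are to "truthfully reflect the changes in the condition after taking LIPUS" (LIPUS is evidently the study ultrasound).
- Item (2): adverse reactions and unexpected toxic effects, "regardless of whether they are related to LIPUS or not, should be recorded in detail". It then names the safety statistic: "The incidence of adverse reactions should be counted".
- Item (3): for adverse reactions during the study, "their relevance to LIPUS treatment should be evaluated".
- Item (5): for any serious adverse event in the study, sites must "report to the sponsor within 24 hours or no later than the 2nd working day".

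Section 3.5 leaves physicians and patients aware of the assignment and masks only those who collect primary outcome data.

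**The concern.** An adverse event definition should not depend on cause, so that both arms are observed and counted by one rule and cause is judged afterwards. Section 6.1 puts the cause into the definition. A control patient has had no study intervention to react to, so a site that works from 6.1 has no reason to log that patient's symptoms. A site that works from 6.3(2) would log them. The same control patient could therefore have an event at one centre and none at another.

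The wording of 6.3(1) and of the counted statistic leans towards the device. The person who judges relatedness probably knows the arm. The error could run either way. Background events after PCI might be logged more fully in the ultrasound arm, which would look like harm. Real device effects might instead be put down to the procedure and left out of the count. Sections 7.2 and 7.3 provide no data monitoring committee and no audit, so site recording carries much of the safety oversight.

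**Working it through.** The protocol gives no adverse event rate and no safety power, so there is no figure to reproduce. The check is a comparison of the rules.

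**Step 1. Which rules could reach a control patient's event?**

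| Section | Rule, paraphrased | Fits a control patient? |
| --- | --- | --- |
| 6.1, definition | Reaction to the intervention | No |
| 6.1, ascertainment | Symptoms and observation at every visit | Yes |
| 6.3(1) | Patient reports changes after the ultrasound | No |
| 6.3(2), recording | Whether or not related to the ultrasound | Yes |
| 6.3(2), statistic | Incidence of adverse reactions | Unclear; depends on how strictly the term is read |
| 6.3(3) | Relatedness assessed for each recorded reaction | Yes, if the term is used loosely |
| 6.3(5) | Any serious adverse event in the study | Yes |

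**Step 2. Do they agree?** No. The definition in 6.1 excludes what the recording rule in 6.3(2) includes, and no precedence is stated. Item (3) makes sense only if something can be called a reaction before its cause is known, so 6.3 does not keep to the meaning in 6.1.

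**Step 3. Who judges cause?** The investigator, under 6.3(3). The only masking in 3.5 is for collection of the primary outcome, so no masking is stated for this judgement.

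**Step 4. Literal-6.1 worst case, for scale only.** Assume that sites ignore 6.3, that every event in the ultrasound arm is counted, that control stays at 0, and that the true background rate is the same in both arms. Take 100 per group (section 3.4). The rates below are assumptions and have no basis in the documents.

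- Two-sided Fisher P for k versus 0 with 100 per arm is 2 × C(100,k) / C(200,k).
- k = 5: 2 × 75,287,520 / 2,535,650,040 = 0.059.
- k = 6: 2 × 1,192,052,400 / 82,408,626,300 = 0.029. So six events is the smallest count with P below 0.05.
- The chance of a spurious excess is P(X ≥ 6), where X is binomial with n patients and the background rate. With 80 per arm the threshold is also six (P = 0.028).

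| Assumed background rate | 100 per arm | 80 per arm |
| --- | --- | --- |
| 2% | 1.5% | 0.5% |
| 5% | 38% | 21% |
| 10% | 94% | 82% |
| 20% | about 100% | 99.9% |

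This is an upper bound under a reading that 6.3(2) contradicts. It does not predict what this trial would show.

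**Step 5. The two limits in 6.3(5).** For an event on a Friday, 24 hours ends on Saturday. The second working day is Monday if Friday counts as the first, and Tuesday if it does not. The sentence does not say which limit binds.

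**The case against.** A reader might infer from 6.1 that control patients can have no adverse events and that any safety comparison between arms is uninterpretable. The documents do not support either conclusion.

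- Section 6.3(2) requires recording whatever the relation to the device, 6.3(5) covers any serious event in the study, and ascertainment in 6.1 is not tied to an arm. Control events can be recorded.
- Because 6.3(3) evaluates relatedness after something has been called a reaction, the counted incidence may include unrelated events. The count does not necessarily require attribution to the device.
- Safety is not among the aims in section 2 or the outcomes in 3.9, and no between-arm safety test is named. Tabulation may properly sit in an analysis plan that is not shown.
- Acute stent thrombosis, malignant arrhythmia and acute left heart failure are named only as withdrawal reasons in 3.3.2, but would ordinarily be caught by the grading in 6.2 and by 6.3(5).
- Section 7.1 provides ongoing monitoring by a day-to-day team with weekly meetings, so site recording is not the only safeguard.
- The sentence in 6.3(5) can be read as a target followed by an outer limit.

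All of this stands, and it limits the point. It does not remove the contradiction, because a definition belongs in the protocol, the one given conflicts with the recording rule, and loose use of the word reaction leaves each site to choose its own reading.

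**Conclusion.** The point holds as an internal contradiction that risks unequal ascertainment and counting of adverse events between arms. It rests on the wording of 6.1 against 6.3(2), the device-centred wording of 6.3(1), and the absence of stated masking for the causality judgement. It does not show that control events go unrecorded, and it does not touch the primary analysis.

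The size of any distortion cannot be derived from the documents. The literal-6.1 figures apply only if 6.3 is ignored and only at the assumed rates. The matter should be corrected, because the safety record of an open-label trial depends on one rule for both arms. The unclear limit in 6.3(5) is a separate and smaller inconsistency.

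**What to change.** - **6.1:** define an adverse event as any untoward medical occurrence in either arm from randomisation to the end of follow-up (month 3), whether or not related to the device. Keep adverse reaction for events judged related.
- **Relatedness:** record it as a separate field, after the event has been logged.
- **6.3(1):** reword it to apply to both arms, with the same form and the same visit schedule.
- **6.3(2):** count all adverse events and all serious adverse events by randomised arm, and list device-attributed reactions separately for the ultrasound arm.
- **6.3(5):** reconcile the two reporting limits so that sites can tell which one binds.

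The cost is protocol wording, the ethics approval that section 7.4 requires for any modification, a common form, and slightly more recording in the control arm. The sample size and the efficacy analysis do not change.

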**6.2 Grading of the degree of adverse events**

The investigator assesses the severity of the AE according to CTCAEV5.0:

Grade 1: mild, asymptomatic, or mild; Seen clinically or diagnostically only; No treatment is required;

Grade 2: moderate, requiring smaller, topical or non-immersion treatment, age-appropriate instrumental daily activities (ADLs) limitation (instrumental ADLs refer to cooking, buying clothes, using the phone, managing money, etc.);

Grade 3: Severe or medically significant but not immediately life-threatening; resulting in hospitalization or prolongation of hospitalization; Disability; Limitation of self-rational activities of daily living (self-responsible activities of daily living refer to bathing, dressing and undressing, eating, washing, taking medication, etc., and not being bedridden;

Grade 4: life-threatening, requiring urgent treatment;

Grade 5: AE-related death.

**6.3 Methods for recording and reporting adverse events**

(1) The investigator should explain to the patient that it is necessary to truthfully reflect the changes in the condition after taking LIPUS and avoid inducing questions.

(2) While observing the efficacy, pay close attention to the observation of adverse reactions or unexpected toxic side effects (including symptoms, signs, laboratory examinations), regardless of whether they are related to LIPUS or not, should be recorded in detail, and the causes should be analyzed, judgments should be made, and follow-up observation and records should be followed. The incidence of adverse reactions should be counted.

(3) For adverse reactions occurring during the study, the symptoms, severity, occurrence time, duration, treatment measures, and process should be recorded in the study medical record, and their relevance to LIPUS treatment should be evaluated, and recorded in detail by the investigator, signed and dated.

(4) When adverse reactions are found, the observer physician can decide whether to suspend the observation according to the condition, and the cases that withdraw from the trial due to adverse reactions should be followed up and investigated, and the treatment process and results should be recorded in detail.

(5) If there is a serious adverse event in the study, the unit undertaking the clinical study must take immediate measures to protect the safety of the subjects and report to the sponsor within 24 hours or no later than the 2nd working day. The Sponsor will ensure that all reporting procedures required by laws and regulations are met.

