**3 Study program**

**3.1 Study design and ethical approval**

This nonblinded, multicenter, parallel-group, randomized (1:1) controlled study will be conducted in 10 large hospitals in China, including Qilu Hospital of Shandong University, Qingdao Municipal Hospital, Yantai Yuhuanding Hospital, Linyi People’s Hospital, Tengzhou Central People’s Hospital, Weifang People’s Hospital, Jining No.1 People’s Hospital, Weihai Central Hospital, Liaocheng People’s Hospital, Dongying People’s Hospital, and Qilu Hospital of Shandong University (Qingdao). These hospitals were selected because of their significant experience and ability to recruit for PCI in cardiology as well as their ability to collaborate across disciplines to ensure that patients receive comprehensive treatment and rehabilitative support. The study protocol was reviewed and approved by the Ethics Committee of Qilu Hospital of Shandong University and other participating institutions (Ethics Committee reference number KYLL-202308-006). The study was registered on ClinicalTrials.gov, ID: NCT06640400.

Participants in this study will be recruited from the aforementioned medical institutions. Inclusion criteria call for hospitalized patients diagnosed (through laboratory and imaging tests) with CAD requiring PCI ^[16]^. Following consent from the patients or their family members, screening procedures will be conducted by medical professionals to ensure compliance with the eligibility criteria. Only those individuals meeting all recruitment criteria and no exclusion criteria will be included in the study.

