**7 Oversight and monitoring**

**7.1 Composition of the coordinating center and trial steering committee**

Ongoing clinical monitoring will be overseen by a day-to-day management team comprising the principal investigator (PI), a doctoral student, a research coordinator, and an assistant manager. Regular weekly meetings will be held by the group to ensure effective coordination and management of the study. This trial does not have a trial steering committee.

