**7.2 Composition of the data monitoring committee—its role and reporting structure**

No formal data monitoring committee has been established for this trial, as there are no interim analyses or planned procedures for early stopping.

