**7.3 Frequency and plans for auditing trial conduct**

Not applicable. No auditing is planned in this trial. The PI will meet weekly during the study period to review trial progress.

**7.4 Plans for communicating important protocol amendments to relevant parties (e.g., trial participants, ethical committees)**

Any proposed modifications to the study protocol require prior approval from the Ethics Committee of Qilu Hospital of Shandong University. Upon approval, these protocol amendments must be documented in the trial register and, for transparency and accuracy, integrated into the final research report.

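### Section 6.3(5) offers a second-working-day alternative to its 24-hour limit for serious adverse events, so a Friday-evening event may reach the sponsor about 72 to 96 hours later and still comply

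*Protocol*

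**What the plan says.** The only deadline for serious adverse events is in Protocol section 6.3, item (5). The site "must take immediate measures to protect the safety of the subjects" and must "report to the sponsor within 24 hours or no later than the 2nd working day". The item ends with the sponsor's onward duty: "The Sponsor will ensure that all reporting procedures required by laws and regulations are met".

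The surrounding oversight is thin. Section 3.1 says the trial "will be conducted in 10 large hospitals in China" (it then lists eleven names, which does not affect this point). Section 7.1 states "This trial does not have a trial steering committee", section 7.2 states "No formal data monitoring committee has been established for this trial" and section 7.3 states "No auditing is planned in this trial". Sections 7.1 and 7.3 do provide for a small management team, including the principal investigator, that meets weekly.

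**The concern.** An 'or' between a strict and a loose deadline leaves the loose one in force. The working-day clause is worded as an outer limit ("or no later than the 2nd working day"), so a report made on that day is on time whatever has happened to the 24 hours. Nothing in the sentence says which limit applies when they differ. It also does not say whether the clock runs from the event or from the site's awareness of it, or whether the day of the event is working day 1. No other section settles these questions.

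What is at stake is the speed at which a safety signal at one hospital becomes known centrally. Section 3.3.3 lists serious safety problems as a ground for stopping the trial, and action across sites on that ground needs central knowledge. With no data monitoring committee, steering committee or auditing, the site's report to the sponsor is the only cross-site safety reporting that carries a stated deadline. Treatment is also dense: section 3.7.2 sets two sessions a day for 10 days, 20 in all, after a baseline taken 24 hours after PCI. A few days is therefore a sizeable part of a course for patients under treatment elsewhere.

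**Working it through.** **Inputs from the Protocol.** Two alternative limits, 24 hours and the second working day (section 6.3(5)); two sessions a day, 20 in total (section 3.7.2).

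**Assumptions, not in the Protocol.** Working week Monday to Friday; no public holiday; clock starts at the event; event and report at the same time of day. Because the counting rule is not given, both readings are shown.

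**Formula.** Latest compliant delay = (calendar days from the event to the second working day) × 24 h.

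| Day of event | Event day is working day 1 | Event day not counted |
|---|---|---|
| Monday | Tue: 1 × 24 = 24 h | Wed: 2 × 24 = 48 h |
| Tuesday | Wed: 1 × 24 = 24 h | Thu: 2 × 24 = 48 h |
| Wednesday | Thu: 1 × 24 = 24 h | Fri: 2 × 24 = 48 h |
| Thursday | Fri: 1 × 24 = 24 h | Mon: 4 × 24 = 96 h |
| Friday | Mon: 3 × 24 = 72 h | Tue: 4 × 24 = 96 h |
| Saturday | Tue: 3 × 24 = 72 h | Tue: 3 × 24 = 72 h |
| Sunday | Tue: 2 × 24 = 48 h | Tue: 2 × 24 = 48 h |
| Days above 24 h | 3 of 7 | 7 of 7 |

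For a Friday event, 72/24 = 3 and 96/24 = 4 times the 24-hour limit.

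**Sensitivity to clock times.** Let the event fall on Friday between 17:00 and 22:00, and let the deadline day end at 17:00 or at midnight.

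- Deadline on Monday: from 67 h (22:00 to Monday 17:00) to 79 h (17:00 to Monday midnight).
- Deadline on Tuesday: from 91 h to 103 h on the same end points.
- Midweek comparison, event on Tuesday at 18:00: 23 to 30 h if Tuesday counts, 47 to 54 h if it does not.

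The 72 to 96 h range is therefore a fair central statement. A public holiday would lengthen it.

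**What the delay means in sessions.** If treatment continues daily, a patient at another hospital receives 2 × 1 = 2 sessions in 24 h, 2 × 3 = 6 in 72 h and 2 × 4 = 8 in 96 h. As shares of the 20-session course these are 2/20 = 10%, 6/20 = 30% and 8/20 = 40%.

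**After the fix.** With a single 24-hour limit, an event the site learns of on Friday at 18:00 must be reported by Saturday at 18:00. Under the current wording the same event may be reported 71 h later (Monday 17:00) to 102 h later (Tuesday midnight).

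**The case against.** The strongest reply concerns weight. The affected patient does not depend on the sponsor's knowing: section 6.3(5) demands immediate local action, and sections 6.3(4) and 3.3.2 let the physician or investigator suspend or withdraw. That stands, and it limits the point to cross-site awareness.

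The sentence can also be read as a 24-hour target with a backstop for non-working days. If the day of the event counts as day 1, Monday-to-Thursday events keep a limit of about 24 hours, so on four days of seven little is lost. That is correct on that reading. But the Protocol does not choose it, and even then all Friday and weekend events exceed 24 hours.

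Central oversight is not absent either, since a management team meets weekly. However, no deadline for serious adverse events runs through those meetings, and a weekly interval (7 × 24 = 168 h) is longer than 96 h. The sponsor's promise to meet its regulatory reporting duties does not shorten the site's own limit.

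Finally, the Protocol rates the study as low-risk and expects only mild local reactions, so serious events may be few and sites may report promptly anyway. This makes harm less likely. It does not make the rule clear.

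**Conclusion.** The concern holds. As written, the second working day is the outer limit, and the 24-hour limit does not bind whenever the two differ. A site can follow the rule exactly and report a Friday-evening event about 72 to 96 hours later. Allowing for different clock times, the range is 67 to 79 h if Friday counts as day 1 and 91 to 103 h if it does not. These figures rest on a two-day weekend, no holiday and a clock that starts at the event. If the clock starts at awareness, any time before the site learns of the event is added to the delay.

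This is a defect in safety-reporting wording of moderate weight. It has no bearing on sample size, power, alpha or the analysis. It deserves correction because the rule slows the one dated route by which a signal passes between hospitals, and because correcting it is cheap.

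**What to change.** In section 6.3(5), replace the reporting phrase with: *report to the sponsor within 24 hours of the site becoming aware of the event*. Delete the second-working-day alternative. This sets one limit and one clock start, and it removes the question of how working days are counted.

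The cost is one sentence of protocol wording, approved through the amendment route in section 7.4, and a notice to sites. The downside is that sites may have to report at weekends and on public holidays. During the treatment period this should be manageable, because patients are in hospital with daily contact (sections 3.8 and 4.3).
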